### Qualitative interviews

A rapid qualitative approach will be used to ensure findings from the pilot trial process evaluation can inform the future optimisation trial in a timely manner
^
45,
46
^. Semi-structured interviews with trial participants and therapists will last up to one hour, will be conducted
*via* telephone or videoconferencing software (
*e.g.*, Microsoft Teams), and will be recorded. During the interview, the interviewer will take notes. Immediately following each interview, the interviewer will complete an individual Rapid Research Evaluation and Appraisal Lab Rapid Assessment Procedure (RREAL RAP) sheet for the participant. RREAL RAP sheets are a two-column table summarising the information collected in an interview. Different RREAL RAP sheets will be used for therapists and participants.

**
*Trial participants*
**. Semi-structured interviews will assess fidelity of receipt and enactment, acceptability of the intervention components, and barriers and facilitators to recruitment and retention in the trial. Questions will be based on the NIH fidelity domains, the TFA, and the TDF. Interview guides have been reviewed and amended based on suggestions from our patient and public involvement group (participant interview questions can be found as
*Extended data*
^
47
^).

**
*ACT therapists*
**. Semi-structured interviews with therapists will assess fidelity of training and delivery and any barriers to these, relationship building with participants in the intervention component, and acceptability of the ACT component (therapist interview questions can be found as
*Extended data*
^
47
^). We will also explore any suggested improvements to the intervention component and establish whether it may be implementable in routine care in the NHS.

### Data analysis plan

**
*Quantitative analysis*
**

Intervention fidelity. Descriptive statistics will summarise the quantitative intervention component fidelity assessments (
Table 2). For the ACT component, these will also be presented by site. Specific to the fidelity of design assessment, the first-order agreement coefficient statistic (AC1) will estimate the interrater reliability between the independent coders and the BCTs that the components intended to target
^
21,
39
^. Strength of fidelity of design will be defined in terms of pre-established AC1 thresholds; <0.2=poor, 0.2 ≤ 0.4=fairly poor, >0.4 ≤0.6=moderate, >0.6 ≤0.8=good, >0.8 and ≤ 1=very good
^
48
^. Discrepancies will be resolved through discussions between SG and the coders.

Intervention component acceptability. Descriptive statistics will be calculated for the individual items on the acceptability questionnaire, and overall, for each intervention component. Additional questions regarding the acceptability of specific aspects of the ACT and SMS components will be summarised. All summaries will be presented by component. Missing data will be summarised.

Barriers and facilitators to recruitment and retention of participants. Descriptive statistics will be presented for the RN barriers to recruitment and retention questionnaire, alongside qualitative data from the questionnaire. Summaries will be presented overall and by site. Missing data will be summarised.

Participant experience of trial participation. Descriptive statistics will be presented (1) for overall trial experience, and split by experience before starting the trial, during the trial and at the end of the trial; (2) for the one item of the AQ aimed at assessing general acceptability of the trial overall, by experimental condition and by site. Missing data will be summarised.

*

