## Protocol

### Aims and objectives

This process evaluation has three aims: to assess (1) the fidelity of the intervention components; (2) the acceptability of the intervention components; (3) participant’s experience, and barriers and facilitators to recruitment and retention in a fractional factorial trial. These aims address the implementation and contextual factors themes outlined in the MRC framework
^
23
^. The specific objectives for each aim are:

1.Fidelity; Establish the fidelity of each intervention component across five domains of fidelity, guided by the NIHBCC fidelity framework
^
32
^:a.Design. To establish to what extent the intervention components target the behaviour change techniques (BCTs) they are intended to, and to what extent the components are distinct from one another;b.Training. To evaluate the adequacy of therapist training for the delivery of the intervention;c.Delivery. To assess if each intervention was delivered as planned;d.Receipt. To evaluate if participants receive and understand the intervention components they were allocated to;e.Enactment. To understand the degree to which participants implement the intervention components in their daily life;

Identify barriers to the fidelity of training, delivery, receipt and enactment of the intervention components, including any influential contextual factors.

2.Acceptability:a.Assess the acceptability of each intervention component3.Trial experience, recruitment and retention:a.Establish the barriers and facilitators to recruitment and retention of participants;b.Evaluate participant experience of trial participation.

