	ACT	Printing of ACT module booklet	Questionnaire	Participant	4 months
	Website	Website usage	Website Online System	-	2 and 4 months
	All	Understanding and receipt of the intervention component	Qualitative interview	Participant	End of trial
**Enactment.** To understand the degree to which participants implement the intervention components in their daily life.	All	Qualitative data	Qualitative interview	Participant	End of trial
Identify barriers to the fidelity of training, delivery, receipt and enactment of the intervention components, including any influential contextual factors.	All	Qualitative data	Semi-structured interview	Participants and therapists	End of trial

Key: BCT= Behaviour Change Technique. BCTTv1 = Behaviour Change Technique Taxonomy version 1. ACT = Acceptance and Commitment Therapy. ACT-FM: Acceptance and Commitment Therapy Fidelity Measure. SMS = Short Message Service. CRF = Case Report Form.

Fidelity of design. We will assess whether the intervention components show fidelity to the intended design, in terms of BCTs. BCTs are considered ‘active ingredients’ of behaviour change interventions (e.g. problem solving, action planning). They can be coded using the behaviour change taxonomy version 1 (BCTTv1), which contains 93 BCTs
^
37,
38
^. The research team (SG, SS, LH and CG) have coded which BCTs are present for each intervention component
^
21
^. Two independent coders, external to the research team, will also code the intervention components. Coders will be provided with all intervention component materials and a coding manual and will be asked to identify which BCTs from the taxonomy are present in each intervention component. This process will be conducted once the trial has begun recruitment. The coders will have experience in using BCTs and will have completed BCTTv1 training. They will only code whether a BCT is present or absent, not the frequency of occurrence. Coding from the independent coders will be compared to the original coding
^
21
^, and an agreement coefficient will be calculated
^
39
^. All discrepancies will be discussed between one member of the research team (SG) and the two independent coders, and a final code list will be produced.

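### If all 93 taxonomy items are counted, the AC1 bands that define design fidelity can grade a component very good when a coder finds none of its intended techniques

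*Protocol article*

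**What the plan says.** Objective 1a (Aims and objectives) has two parts: whether each component targets the BCTs it was meant to target, and "to what extent the components are distinct from one another".

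Under Fidelity of design, the taxonomy is described as one "which contains 93 BCTs". Two coders from outside the research team "will be asked to identify which BCTs from the taxonomy are present in each intervention component". The rating is binary: "They will only code whether a BCT is present or absent, not the frequency of occurrence". Then "Coding from the independent coders will be compared to the original coding". Discrepancies are discussed between one research team member and the two coders, and a final code list results.

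The Data analysis plan names the statistic: "the first-order agreement coefficient statistic (AC1) will estimate the interrater reliability between the independent coders and the BCTs that the components intended to target". It then makes the bands of that coefficient the definition of the result: "Strength of fidelity of design will be defined in terms of pre-established AC1 thresholds". The top band is ">0.8 and ≤ 1=very good". Below it, values above 0.6 and up to 0.8 are good, values above 0.4 and up to 0.6 are moderate, and values under 0.2 are poor.

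The article does not state how many BCTs each component was intended to contain, or which items enter AC1.

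**The concern.** The first part of objective 1a is about positives: of the techniques a component was built to contain, how many does an independent reader recognise? AC1 weighs agreement on absence and agreement on presence alike. When a component uses only a few of 93 techniques, nearly all agreement is that the other techniques are absent. AC1's chance correction is small at low prevalence, so it removes little of that agreement. The coefficient can then sit near 1 whatever share of the intended techniques was recognised.

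At stake is a published label. The fidelity findings are meant to guide improvements to the components before the optimisation trial, and a label that stays favourable through a complete miss gives false reassurance on the point being tested.

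**Working it through.** The article states no AC1 value, so there is no figure to reproduce. The check is what the stated rule returns in defined cases.

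**Inputs.** N = 93 items per component (taxonomy size from Fidelity of design; its use as the AC1 item set is an assumption). Binary codes (same section). *Very good* means AC1 above 0.8 (Data analysis plan). k, the number of intended BCTs in a component, is not given and is varied.

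**Formula, two raters (intended coding and one coder).** Let a = BCTs in both lists, b = intended only, c = coded only.

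- Observed agreement: Pa = (N − b − c)/N
- Mean prevalence: π = (2a + b + c)/(2N)
- Chance term: Pe = 2π(1 − π)
- AC1 = (Pa − Pe)/(1 − Pe)

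**Case 1: the coder finds none of the k and codes nothing else** (a = 0, b = k, c = 0). For k = 5:

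- Pa = 88/93 = 0.946
- π = 5/186 = 0.027
- Pe = 0.052
- AC1 = (0.946 − 0.052)/0.948 = 0.943

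**Case 2: the coder finds none of the k and codes k other BCTs** (a = 0, b = c = k). For k = 7:

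- Pa = 79/93 = 0.849
- π = 7/93 = 0.075
- Pe = 0.139
- AC1 = (0.849 − 0.139)/0.861 = 0.825

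| k | Case 1: AC1 and grade | Case 2: AC1 and grade |
|---|---|---|
| 3 | 0.967 very good | 0.931 very good |
| 5 | 0.943 very good | 0.880 very good |
| 7 | 0.919 very good | 0.825 very good |
| 8 | 0.906 very good | 0.796 good |
| 10 | 0.880 very good | 0.734 good |
| 13 | 0.839 very good | 0.632 good |
| 14 | 0.825 very good | 0.596 moderate |
| 15 | 0.811 very good | 0.558 moderate |
| 16 | 0.796 good | 0.519 moderate |

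A complete miss is therefore graded *very good* up to k = 15 in case 1 and up to k = 7 in case 2. Case 1 stays *good* up to k = 27 (0.614) and is *moderate* at k = 28 (0.596). Cohen's kappa is 0.00 throughout case 1 and slightly negative in case 2 (−0.08 at k = 7).

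**Half matched, k = 10** (a = b = c = 5). Pa = 83/93 = 0.892, π = 10/93 = 0.108, Pe = 0.192, so AC1 = 0.87, *very good*. Positive agreement is 2a/(2a + b + c) = 10/20 = 0.50, and kappa is 0.44.

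**Three raters** (intended coding plus both coders, neither finding any intended BCT or coding others). AC1 remains above 0.8 up to k = 23 (0.806).

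**Sensitivity to the item set** (case 1).

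| Items in AC1 | k = 5 | k = 10 |
|---|---|---|
| 93 | 0.943 | 0.880 |
| 40 | 0.858 | 0.680 |
| 30 | 0.803 | 0.538 |
| 20 | 0.680 | 0.200 |

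If only BCTs coded by at least one party are counted, a complete miss gives AC1 = −1. The grade depends heavily on a choice that the article does not state.

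**The case against.** **The deciding inputs are not documented.** Neither k nor the AC1 item set appears in the article, which summarises a fuller protocol that may fix both. This stands as a limit on confidence. It does not remove the point: coders work from the whole taxonomy, so 93 is the natural reading, and the role of the bands is written in the article itself.

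**The rule can return lower grades.** A reader might infer that it cannot return an unfavourable verdict for realistic components, or that the grade is good or better whatever the coders find. The figures do not support that. Disjoint sets give *moderate* from k = 14. A coder who misses all 10 intended BCTs and names 20 others gives 0.558, the same total of 30 mismatches as k = 15 in case 2. The failure is confined to small sets of intended and coded techniques.

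**Misses would surface anyway.** A reader might infer that a component lacking its intended techniques would enter the optimisation trial unchanged. The documents do not support that either. Every missed BCT is a discrepancy to be discussed, a final code list is produced, and quantitative and qualitative data are combined narratively to improve components. These safeguards stand, but none of them alters the AC1 grade.

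**Little hangs on it.** The Discussion bases progression on consent rates, component adherence and availability of outcome data. Design fidelity is not among them. This stands and limits the severity.

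**Distinctness.** AC1 against the intended codes does not compare components with each other, but it is not presented as doing so. Table 2 lists the BCTs coded for each component and the analysis plan summarises Table 2 descriptively, so overlap can be described from those lists. No error is claimed there.

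**Conclusion.** The point holds conditionally. If all 93 items enter AC1 for each component, the stated rule can grade design fidelity *very good* when a coder recognises none of the intended BCTs: up to 15 intended BCTs if nothing else is coded, and up to 7 if as many wrong ones are coded. Larger sets bring the grade down to *good* or *moderate*, and a smaller item set weakens the effect. The grade therefore does not reliably answer the first part of objective 1a and may reassure falsely.

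Confidence is moderate, because k and the item set are assumptions. The severity is limited: this is one descriptive label in a pilot process evaluation, with item-by-item discussion behind it and no progression decision attached. It is worth correcting before the codes are analysed, but it does not threaten the trial.

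**What to change.** For each component and each independent coder, using the codes as they stood before discussion, base the statement of design fidelity on three figures with 95% CIs:

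- the proportion of intended BCTs that the coder identified, a/(a + b);
- the proportion of coded BCTs that were intended, a/(a + c);
- positive agreement, 2a/(2a + b + c).

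Keep AC1 as a secondary figure, state which items enter it, and drop the verbal bands. Optionally, describe the pairwise overlap of the coded BCT sets between the four components for the distinctness part of the objective.

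The cost is a change of analysis wording; the same codes are used. The denominators are small, so the intervals will be wide, and the reported fidelity may look less favourable than an AC1 band would.

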**Qualitative analysis**
*. Individual RREAL RAP sheets completed immediately after the interview will be collated into higher level RREAL RAP sheets; one per component for data relating to intervention component acceptability and fidelity, one overall for data relating to participant trial experience, and one overall for therapist interview data
^
45,
46,
49
^. Regular team meetings will review emerging findings, changes to the interview schedule or RREAL RAP sheets, and data sampling. The interviews will be recorded and selectively transcribed verbatim. Specific quotes will be extracted from the transcripts and added to the RREAL RAP sheets to inform analysis. For each overall aim (fidelity, intervention component acceptability, and trial experience), the relevant quantitative and qualitative data will be combined narratively to determine whether the intervention components could be delivered with fidelity overall, whether each intervention component was acceptable to women with breast cancer, and whether the experience in the trial was acceptable to women with breast cancer, or if there were barriers to recruitment and retention within the pilot trial. Together these findings will be used to make improvements to the intervention components and trial processes, should these be necessary.

### Ethics and dissemination

The study has been approved by Wales Research Authority Research Ethics Committee 3 (21/WA/0322) and is a registered clinical trial (ISRCTN registry,
ISRCTN10487576, 16/12/2021). It is sponsored by the University of Leeds (
[contact]). Amendments to the protocol will be submitted to the ethics committee, and if approved, communicated to research sites. Study findings will be disseminated through peer-reviewed publications. At the end of the trial, all data held by the CTRU and all trial data will then be securely archived at the University of Leeds for a minimum of 5 years. This paper is a summary of protocol version 3.0 (18/08/2022).

### Trial status

The study opened for recruitment on the 20th of May 2022 and was open at the time of submission.

## Discussion

This paper describes the design and methods of a process evaluation embedded in the ROSETA pilot trial. This process evaluation aims to investigate whether four intervention components can be delivered with fidelity, whether the intervention components are acceptable to participants and trial therapists, and to explore participant’s experiences in the trial along with barriers and facilitators to recruitment and retention. Given there is little guidance available for the conduct of process evaluations within factorial trial designs, our protocol may guide others seeking to conduct similar process evaluations.

The results of this process evaluation will be used to adapt and improve the intervention components where necessary, should progression criteria to a larger optimisation trial be met. Our progression criteria to progress to a full optimisation trial are based on predefined criteria for consent rates, intervention component adherence, and availability of outcome data. These are described in detail elsewhere
^
22
^. The full optimisation trial would aim to identify the most effective combination of intervention components to support medication adherence in women with early stage breast cancer, without exceeding a pre-specified cost of £3397 per patient, based on health economic modelling
^
21
^.

This process evaluation has the potential to highlight key issues in the specific intervention components in terms of fidelity and acceptability, and regarding the overall trial design and its implementation within an NHS setting. As factorial designs are relatively uncommon in behavioural trials, we hope that this process evaluation can offer useful insights for others.

## Data Availability

No data are associated with this article. Open Science Framework: ROSETA Pilot Trial Process Evaluation.
https://doi.org/10.17605/OSF.IO/8DWRN
^
47
^. The project contains the following extended data: Participant Interview Guide Therapist Interview Guide Data are available under the terms of the
Creative Commons Zero "No rights reserved" data waiver (CC0 1.0 Public domain dedication).
